## Abstract

**Background:**

Mild cognitive impairment (MCI) is known as a transitional status between normal cognitive function and Alzheimer’s disease (AD). Acupuncture and Chinese herbal medicines (CHMs) are considered to be beneficial to patients with cognitive impairment. However, it is still unknown whether the combination of the two therapies could optimize the therapeutic effect for MCI. This trial is aimed to evaluate the therapeutic effects of acupuncture and the herbal formula *Yishen* Granule (YSG) for elderly patients with MCI.

**Methods/design:**

This is a multi-sited, patient-blinded, randomized controlled trial (RCT). Two hundred and forty eligible patients will be randomly divided into four groups: A. acupuncture with YSG, B. acupuncture with placebo herbal medicine, C. sham acupuncture with YSG or D. sham acupuncture with placebo herbal medicine. Acupuncture treatment will be given twice a week for 8 weeks and then once a week for 4 weeks. The herbal treatment patients will be given granules daily for 12 weeks, 8 weeks of standard-dose followed by 4 weeks of mid-dose. The primary outcome is scored by the Montreal Cognitive Assessment (MoCA). The secondary outcomes will be scored by the Mini-Mental State Examination (MMSE) and event-related potential (ERP). All the assessments will be conducted at baseline, and at the eighth and 12th week after intervention starts. The follow-up assessments will be performed with the MoCA in the 12th, 24th, and 36th weeks after intervention ends. Intention-to-treat (ITT) analysis will be used in this RCT.

**Discussion:**

This RCT will provide us information on the effect of treating MCI patients with only acupuncture, herbal formula as well as the combination of both. The additive effect or synergistic effect of acupuncture and Chinese herbal formula will then be analyzed.

**Trial registration:**

This trial is registered with ChiCTR-INR-17011569 on 5 June 2017, and has been approved by the Ethics Committee of Shanghai Municipal Hospital of Traditional Chinese Medicine (2017SHL-KY-05).

**Electronic supplementary material:**

The online version of this article (10.1186/s13063-019-3212-z) contains supplementary material, which is available to authorized users.

## Background

Dementia is inevitably associated with an aging population. The progressive deterioration of cognitive function increasingly interferes with daily activity in the elderly [1]. Worldwide, nearly 25 million people have been diagnosed with dementia, which is a major public health problem [2]. In recent years, with the increasing trend of an aging population, the prevalence of dementia has increased year by year. Alzheimer’s disease (AD) is one of the major sub-types of dementia among the population aged 60 years and older in China, and the prevalence of AD increased significantly from 1980 to 2004 [3].

Mild cognitive impairment (MCI) is known as a transitional status between normal cognitive function and clinically probable AD [4]. People with MCI constitute a high-risk group for AD and showed increasing prevalence among older age groups [5]. Subjective cognitive complaints has been regarded as one of the most common presenting symptoms of cognitive impairment, and a prevalence rate of 31.40% for MCI was found in adults aged 50 years and older with subjective cognitive complaints [6]. Effective interventions may attenuate the MCI and the potential risk of a deterioration of the MCI [7]. At present, no pharmacological treatment has demonstrated convincing effects in delaying longer-term progression or conversion to dementia [8].

Acupuncture, a Traditional Chinese Medicine treatment, has been widely used in clinical practice for several thousand years, including nervous system disorders. Basic studies have reported that acupuncture may have effects on multi-infarct dementia and AD via improving memory ability [9, 10]. Several clinical trials have shown that acupuncture at specific acupoints such as *Taichong* (LR3), *Hegu* (LI4), and *Taixi* (KI3) can activate certain cognitive-related regions of the brain in patients with MCI [11, 12]. Moreover, different insertion depths and acupoints may exert different effects [13, 14]. A systematic meta-analysis involving 568 subjects pooled from five randomized controlled trials (RCTs) of acupuncture versus nimodipine treatment has shown that acupuncture is beneficial for amnestic mild cognitive impairment (AMCI) and the combination therapy appears to have superior efficacy [15].

Chinese herbal medicine (CHM) has a long history for treating memory disorders too. Many CHMs, such as *Herba cistanches* and *Polygonum multiflorum*, have shown positive therapeutic effects on cognitive impairment [16, 17]. CHMs are usually used in combination. A placebo-controlled randomized trial showed that the Compound Chinese Medicine, *Bushen* capsule, could improve or maintain the general cognitive function of patients with AMCI during a 2-year treatment [18].

Both the acupuncture and CHMs are considered to be useful in the treatment of MCI. However, it is still unknown whether the combination of the two therapies could optimize the therapeutic effect. The aim for this RCT is to clarify the therapeutic effect of acupuncture combined with CHM for MCI.

## Methods/design

### Setting and design

A multi-sited, patient-assessor-blinded, RCT is designed to evaluate the efficacy and safety of acupuncture and the herbal formula, *Yishen* Granule (YSG), for elderly patients with mild cognitive impairment. Eligible patients will be randomly divided into four groups in a 1:1:1:1 allocation ratio, receiving acupuncture with YSG, acupuncture with placebo herbal medicine, sham acupuncture with YSG, or sham acupuncture with placebo herbal medicine. All the participants will be recruited in Shanghai Municipal Hospital of Traditional Chinese Medicine, Shanghai East Hospital, or Jingan District Hospital of Traditional Chinese Medicine. Written informed consent will be obtained from all patients. The primary outcome is scored by the Montreal Cognitive Assessment (MoCA). The secondary outcomes will be scored by the Mini-Mental State Examination (MMSE) and event-related potential (ERP). All the assessments will be conducted at baseline, and at the eighth and 12th weeks after the intervention starts. The follow-up assessments will be performed with MoCA in the 12th, 24th, and 36th weeks after intervention ends. The flowchart of the study process can be seen in Fig. 1, and the timing of treatment visits and data collection can be seen in Fig. 2 and Additional file 1.

**Fig. 1 Fig1:**
[figure not shown]
Flowchart of the trial. Figure shows the flowchart of the study process

**Fig. 2 Fig2:**
[figure not shown]
Standard Protocol Items: Recommendations for Interventional Trials Statement (SPIRIT) Figure. Figure shows the enrollment, interventions, and data collection

#### Inclusion criteria

Patients meeting all of the following inclusion criteria will be included:Aged 65–85 years; male or femaleComplaint of allomnesia, which can be obtained from an informant who knows the patient wellEssentially intact activities of daily livingGlobal Deterioration Scale (GDS) score 2–3, Clinical Dementia Rating (CDR) score = 0.5, MMSE score ≥ 24, Dementia Rating Scale (DRS) score ≥ 123Able to understand and complete the scale evaluationsAgree with the investigation and sign the written informed consent form

#### Exclusion criteria

Participants meeting any one of the following exclusion criteria will be excluded:Participants who are assessed as normal or dementia by the CDRParticipants with a HAMD (Hamilton Depression Scale) score > 8Participants with schizophrenia, schizoaffective disorder, primary affective disorder (including the history of affective disorder), or participants with a severe neural disorder (such as aphasia or agnosia)Participants who were diagnosed with AD, central nervous system infections, post-traumatic dementia, toxic encephalopathy, metabolic encephalopathy, Huntington’s disease, multiple sclerosis or Parkinson’s disease before memory decline, or participants with untreated primary endocrine diseaseParticipants with severe primary disease of the cardiovascular, hepatic, renal, or hematopoietic systemsParticipants suffering from gastrointestinal diseases that affect drug absorption (such as severe dyspepsia, gastrointestinal obstruction, or gastric ulcer)Participants who are allergic to the study granuleParticipants who have taken Western and/or Oriental medicine in the past 4 weeks to improve their cognitive function

### Sample size

The calculation of the sample size in this trial was based on the change of the MoCA score. Referring to the related trial published in *BMC Complement Alternative Medicine* [7], 80% of patients with MCI showed an improvement of at least 12.5% on the MoCA score after acupuncture treatment. We assumed the rate to be 80% with one active and one control intervention, 85% with both active interventions and 60% with both control interventions. Under the assumption of a significant level of 0.05, 80% power, and 20% dropout rate, a total of 240 participants should be recruited for this RCT (60 participants in each group with 1:1:1:1 allocation).

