### Outcomes

#### Primary outcome

The Montreal Cognitive Assessment (MoCA) is a one-page, 30-point test administered in 10 min [21]. The MoCA is a brief cognitive screening tool with high sensitivity and specificity for detecting MCI [21]. The current version tests eight cognitive functions: visuospatial functions, executive functions, memory, attention, and concentration, language, calculations, conceptual thinking, and orientation [22]. The Chinese version of the MoCA test is available from the following official website: https://www.mocatest.org/wp-content/uploads/2015/tests-instructions/MoCA-Test-Chinese_Beijing.pdf. Total scores of MoCA ranges from 0 to 30. A score of 25 or below indicates the possibility of cognitive impairment [22].

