### Statistical analysis

An intention-to-treat (ITT) analysis will be used in this RCT. Data analyses will be performed with the use of the statistical software SPSS20.0. The baseline characteristics of the participants in the four groups will be dealt with using the chi-squared test and Fisher Exact Test for categorical data and analysis of variance for continuous variables. Intragroup comparisons will be performed via the use of paired *t* test. The main effect and the interaction effect of the two interventions will be analyzed by 2 × 2 factorial analysis of variance. The statistical significance is set at *P* < .05. All the *P* values are two-side.

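### The 240 patients and 80% power come from responder proportions in one pair of arms, so the 80% is not the power of the planned 2 × 2 ANOVA of the MoCA score

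*Protocol article*

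**What the plan says.** The article's Sample size section says that the calculation uses the change in MoCA score, but its only effect inputs are proportions. It cites a trial in which "80% of patients with MCI showed an improvement of at least 12.5% on the MoCA score after acupuncture treatment" and continues: "We assumed the rate to be 80% with one active and one control intervention, 85% with both active interventions and 60% with both control interventions". The remaining inputs are given as "Under the assumption of a significant level of 0.05, 80% power, and 20% dropout rate", leading to 240 patients, that is "60 participants in each group with 1:1:1:1 allocation".

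The Primary outcome section describes the MoCA as a scale ("Total scores of MoCA ranges from 0 to 30") and defines no responder threshold.

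The Statistical analysis section says: "The main effect and the interaction effect of the two interventions will be analyzed by" a 2 × 2 factorial analysis of variance. Within-group comparisons use paired t tests. Chi-squared and Fisher tests are named only for baseline characteristics. The section adds that all P "values are two-side".

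**The concern.** A power statement belongs to one endpoint, one contrast and one test. Here both the endpoint and the contrast change between sizing and analysis. The sizing uses the proportion improving by at least 12.5%; the analysis uses means of a 0 to 30 score. The sizing figure matches a comparison of two of the four arms; the analysis estimates two main effects and an interaction from all four.

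The article aims to learn whether the two treatments combine additively or synergistically. A reader needs to know what MoCA difference, and what interaction, 240 patients can detect. The article does not say, and its 80% invites the belief that the factorial tests have that power.

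**Working it through.** **Inputs from the article.** Responder rates: A (both active) 85%, B and C (one active) 80% each, D (both control) 60%. Alpha 0.05 two-sided, power 80%, dropout 20%, 60 per cell. Completers per cell: 60 × 0.8 = 48. Multiplier: 1.960 + 0.842 = 2.802.

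**1. Reproducing 240.** Arcsine formula for A v D:
- h = 2·[arcsin√0.85 − arcsin√0.60] = 0.574
- n = 2 × 2.802² / 0.574² = 47.6, so 48 per arm
- 48 / 0.8 = 60 per arm; 4 × 60 = 240

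The unpooled-variance formula gives 47, then 59, total 236. The pooled formula gives 49, then 62, total 248. The 80% rate of the single-active arms plays no part.

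The other contrasts tried do not give 240 (pooled formula for the first three):

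| Contrast | Total with dropout |
|---|---|
| 80% v 60% | 412 |
| Main effect, 82.5% v 70% | 456 |
| 85% v 80% | 4,532 |
| Four-group chi-square, 3 df | about 269 |

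**2. The protocol's rates applied to the factorial contrasts, responder scale, 48 per cell.** Sum of p(1−p) over the cells: 0.1275 + 0.16 + 0.16 + 0.24 = 0.6875.
- Main effect: (85 + 80)/2 = 82.5% v (80 + 60)/2 = 70%, difference 0.125. SE = √(0.6875 / (4 × 48)) = 0.0598. Power = Φ(0.125/0.0598 − 1.96) = Φ(0.13) = 55% (53% by the pooled two-proportion formula).
- Interaction: 0.85 − 0.80 − 0.80 + 0.60 = −0.15. SE = √(0.6875/48) = 0.1197. Power = Φ(1.25 − 1.96) = 24%.
- A v D, for comparison: 79%.

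The fall from 79% to 55% and 24% takes place within the responder endpoint. It comes from the change of contrast.

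**3. What the score ANOVA can detect with 80% power, 48 per cell.**
- Main effect (96 v 96): 2.802 × √(1/48) = 0.40 SD
- Interaction contrast: 2.802 × √(4/48) = 0.81 SD

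The article gives no SD. For assumed SDs of 2, 3 and 4 points, the main effect is 0.81, 1.21 and 1.62 MoCA points. The interaction is 0.81 SD times the same SDs: about 1.62, 2.43 and 3.24 points.

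**4. An illustrative translation of the rates to a score.** Assume that each rate is the share of a normal score, with equal SD in all cells, lying above one cut point. The probits of 0.85, 0.80, 0.80 and 0.60 are 1.036, 0.842, 0.842 and 0.253.
- Main effect: (1.036 + 0.842 − 0.842 − 0.253)/2 = 0.392 SD
- Interaction: 1.036 − 0.842 − 0.842 + 0.253 = −0.393 SD (unrounded probits)

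| | 48 per cell | 60 per cell |
|---|---|---|
| Main effect | 77% | 86% |
| Interaction | 28% | 33% |

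**The case against.** The strongest reply is that the mismatch of endpoints may do no harm. A score usually carries more information than a responder indicator. Under the normal cut-point assumption, moving from responder to score raises main-effect power from about 55% to 77% at 48 per cell, and to 86% if all 60 per cell contribute, as an intention-to-treat analysis might allow. The stated 80% lies between those two values. This stands: the article does not show that the main-effect ANOVA is underpowered, and the 55% must not be blamed on the use of responders.

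A second reply is that an unseen analysis plan may contain a responder analysis. It may. That would not make 80% the power of the ANOVA. Nor would running the factorial analysis on responders rescue the figure, since its main effects would then have about 55%.

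A reader might also infer that the article leaves two rival primary endpoints to choose between after the data are seen. It does not support that: it names one efficacy analysis between groups, lists no responder outcome, and keeps statisticians blinded to allocation. The responder rate is only a sizing input.

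Finally, a 12.5% rule is awkward on a 30-point scale: from a baseline of 27, 1.125 × 27 = 30.4 exceeds the maximum. The arithmetic is right, but no analysis in the article uses the rule, so it biases no planned result.

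**Conclusion.** The point holds in this form: the stated 80% is not the power of the planned analysis. It belongs to a comparison of responder proportions between two arms, A and D, whereas the plan tests main effects and interaction on the MoCA score. The conflict lies between sections of the article itself and does not depend on any assumed SD.

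The conclusion does not extend to saying that the score ANOVA is underpowered for main effects. Its power cannot be derived without a mean difference and an SD, and may fall on either side of 80%. The interaction is less open: on the protocol's own rates its power is about 24% on the risk-difference scale and 28% to 33% under the normal cut-point assumption, far below 80% on both readings. The 240 should be fixed to the right test in words; nothing here requires more patients.

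**What to change.** - Name the change in MoCA total score as the primary endpoint to which the 2 × 2 ANOVA applies.
- Withdraw the 80% power claim as it stands, or label it as the power of the A v D responder comparison that it matches.
- Restate what 240 patients deliver for the planned test: at 48 completers per cell, 80% power for a main effect of about 0.40 SD and for an interaction of about 0.81 SD. Convert both to MoCA points with a stated and sourced SD.
- Say plainly that power for the interaction, and so for a claim of synergy, is low under the assumed rates.

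This costs a rewritten sample size paragraph and one sentence in the outcome section. The sample size does not change. A supportive responder analysis, and a count of patients whose baseline score leaves no room for a 12.5% gain, are optional.

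### The single 80% power statement names no contrast; on the protocol's own rates it fits only double-active versus double-control, and the planned interaction test has about 24–28% power

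*Protocol article*

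**What the plan says.** The Sample size section of the protocol article starts from an earlier trial in which "80% of patients with MCI showed an improvement of at least 12.5% on the MoCA score after acupuncture treatment". It then sets a responder rate for each type of group: "We assumed the rate to be 80% with one active and one control intervention, 85% with both active interventions and 60% with both control interventions". So A (acupuncture plus YSG) is 85%, B and C (one active treatment each) are 80%, and D (sham plus placebo) is 60%. One power statement follows: "Under the assumption of a significant level of 0.05, 80% power, and 20% dropout rate, a total of 240 participants should be recruited", that is, "60 participants in each group with 1:1:1:1 allocation". No contrast is attached to it.

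The Statistical analysis section fixes the between-group efficacy tests: "The main effect and the interaction effect of the two interventions will be analyzed by" a 2 × 2 factorial analysis of variance. It also says "All the *P* values are two-side". The Abstract and the Discussion both make it an aim to learn whether the combination is additive or synergistic, which is a question about the interaction. The primary outcome is the MoCA, a score from 0 to 30.

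**The concern.** In a 2 × 2 factorial trial, one power figure cannot cover every question. The contrast between both treatments and neither is the largest of those the assumed rates imply. A main effect averages over the other treatment and is smaller here. The interaction is a difference of differences, and its standard error is twice that of a main effect. If the 80% belongs to the largest contrast, it does not carry over to the tests the analysis section plans.

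What is at stake is the reading of a non-significant result. Someone told that the trial has 80% power could take a non-significant interaction as evidence that the two treatments simply add up, when the trial had little chance of detecting the departure from additivity that its own rates assume.

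**Working it through.** **Inputs (Sample size and Statistical analysis sections).** Rates: A 0.85, B 0.80, C 0.80, D 0.60. Two-sided alpha 0.05 (critical value 1.96). Dropout 20%, so 60 × 0.8 = 48 evaluable per group. Power is Φ(|difference|/SE − 1.96), with Φ the standard normal distribution function, unless another form is named.

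**1. Reproducing 240.** For A versus D with unpooled variance, n per group = (1.96 + 0.842)² × (0.85×0.15 + 0.60×0.40)/0.25² = 46.2, so 47. Dividing by 0.8 gives 59 per group, 236 in total. The pooled-variance formula gives 49 per group, or 62 after dropout. Both are close to 60.

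Power at 48 per group:
- Unpooled: SE = √(0.3675/48) = 0.0875; 0.25/0.0875 = 2.86; power 82%.
- Arcsine: 80%.
- Pooled: 79%.

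The other contrasts tried do not lead to 240:

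| Contrast | Needed for 80% power | Power at 48 per group |
|---|---|---|
| B or C vs D (80% vs 60%) | 82 per group, 103 after dropout | 57% (pooled) |
| A vs B or C (85% vs 80%) | 906 per group | 9% (pooled) |
| Main effect (82.5% vs 70%) | 181 per margin | 53% (pooled) |
| Four-group chi-square, 3 df | 54 per group, about 270 in total after dropout | 75% |

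**2. Main effects, responder scale.** Each is (85 + 80)/2 = 82.5% against (80 + 60)/2 = 70%, a difference of 12.5 points. The four binomial variances sum to 0.1275 + 0.16 + 0.16 + 0.24 = 0.6875.
- Stratified by cell: SE = ½√(0.6875/48) = 0.0598; 0.125/0.0598 = 2.09; power 55%.
- Collapsed margins of 96 versus 96, pooled variance: 53%.
- Simulated ANOVA on the 0/1 responder indicator: 55%.
- With all 60 per group: 63% (collapsed) to 65% (stratified).

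**3. Interaction, responder scale.** 85 − 80 − 80 + 60 = −15 points. SE = √(0.6875/48) = 0.1197; 0.15/0.1197 = 1.25; power 24%. The simulated ANOVA also gives 24%. With all 60 per group, 29%.

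**4. MoCA scores, under an assumption.** The documents give no mean change or SD. Assume that each responder rate is the share of a normal MoCA change above one common cut-off, with a common SD. The group means, in SD units above the cut-off, are then 1.036 (A), 0.842 (B and C) and 0.253 (D).
- Main effect: (1.036 + 0.842 − 0.842 − 0.253)/2 = 0.392 SD; SE = √(1/48) = 0.144; ratio 2.71; power 77%. With all 60: SE 0.129; ratio 3.03; power 86%.
- Interaction: 1.036 − 0.842 − 0.842 + 0.253 = −0.393 SD in size (unrounded inputs); SE = √(4/48) = 0.289; ratio 1.36; power 28%. With all 60: SE 0.258; ratio 1.52; power 33%.

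**Summary**

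| Planned test | Responder scale, 48 (60) per group | Scores under the assumption, 48 (60) per group |
|---|---|---|
| Each main effect | 53–55% (63–65%) | 77% (86%) |
| Interaction | 24% (29%) | 28% (33%) |

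**The case against.** The strongest objection concerns the scale. The primary outcome is the MoCA score, and factorial ANOVA and paired t tests are methods for a continuous score; no analysis of a responder indicator is planned. The 53–55% for a main effect is therefore not clearly the power of the planned test. This stands. A reader might infer that each main effect is close to a coin toss, or that nothing but A versus D could reach 80%. The documents do not support either as a general statement: under the normal-change assumption main-effect power is 77% at 48 per group, and it passes 80% if all 60 are analysed.

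Second, the protocol never says that 240 was derived from A versus D, and that calculation would not have needed the 80% rates. This also stands. A versus D is the best match among the contrasts tried, and no more than that.

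Third, the article condenses a fuller protocol, and pairwise comparisons may be described in an analysis plan that is not shown. That is possible, but the point does not rest on an omission. The article itself fixes the rates, alpha, power, dropout and sample size in one section and the factorial tests in another, and the interaction does not have 80% power on those inputs.

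Fourth, intention-to-treat analysis might keep all 60 per group. That raises the interaction only to 29–33%.

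Finally, no passage says that a non-significant result will be taken as proof of no effect. The risk of misreading is a reasonable concern, not something the protocol plans.

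**Conclusion.** The point holds. The one 80% figure is attached to no contrast, and on the stated rates it reproduces only for A versus D on the responder scale (79–82% at 48 per group). It does not describe the planned interaction test, whose power is 24–33% across both scales and both cell sizes examined, although additivity or synergy is a declared aim. At 48 per group the assumed departure from additivity would be missed about three times in four.

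For the main effects the conclusion depends on the scale: well short of 80% on the responder scale (53–65%), near or above it on scores (77–86%) under an assumption that the documents neither state nor contradict. It would go too far to say that the main effects are underpowered whatever the analysis, or that the sponsor is known to have sized the trial on A versus D.

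The assumed interaction is also negative: the rates imply that the combination gives less than the sum of the two separate effects on the risk-difference scale.

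**What to change.** In the Sample size section:

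1. Name the contrast to which the 80% refers. The stated inputs match A versus D; the sponsor should confirm this or give the actual basis.
2. Replace the single figure with power for each planned contrast at 48 evaluable per group, labelled by scale. Main effects: about 54% for responders, and about 77% for MoCA scores if changes are normal with a common SD. Interaction: about 24% for responders and 28% for scores on the same assumption.
3. State that the interaction is not a powered test and will be reported as an estimate with a confidence interval, so that a non-significant interaction is not read as evidence of additivity.

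The cost is wording only. No patients, visits or tests are added, and the sample size stays at 240. The stated power becomes less favourable.
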